## Abstract

Numbers are everywhere, and supporting difficulties in numerical cognition (e.g., mathematical learning disability (MLD)) in a timely, effective manner is critical for their daily use. To date, only low-efficacy cognitive-based interventions are available. The extensive data on the neurobiology of MLD have increased interest in brain-directed approaches. The overarching goal of this study protocol is to provide the scientific foundation for devising brain-based and evidence-based treatments in children and adolescents with MLD. In this double-blind, between-subject, sham-controlled, randomized clinical trial, transcranial random noise stimulation (tRNS) plus cognitive training will be delivered to participants. Arithmetic, neuropsychological, psychological, and electrophysiological measures will be collected at baseline (T0), at the end of the interventions (T1), one week (T2) and three months later (T3). We expect that tRNS plus cognitive training will significantly improve arithmetic measures at T1 and at each follow-up (T2, T3) compared with placebo and that such improvements will correlate robustly and positively with changes in the neuropsychological, psychological, and electrophysiological measures. We firmly believe that this clinical trial will produce reliable and positive results to accelerate the validation of brain-based treatments for MLD that have the potential to impact quality of life.

## 1. Introduction

Mathematical learning disability (MLD), well known as dyscalculia, is a neurodevelopmental disorder that impairs an individual’s ability to learn number-related concepts, perform accurate math calculations, and solve math problems [1]. With a current prevalence of ~7% worldwide [2], MLD persists into adulthood and represents a growing phenomenon. In Italy, its diagnosis increased 160% from 2017 to 2019 [3].

Low numerical competence can prevent high quality-of-life standards throughout development [4,5,6,7], with potential long-term consequences in the professional, psychological, and social arenas. Low mathematical abilities correlate highly with poorer academic and working success [8,9], restricted use of health resources [10,11,12], worse socioeconomic status, and individuals with MLD usually experience considerable amounts of stress and negative feelings in educational settings. When MLD is not recognized and treated, negative school experiences and a repeated lack of success in mathematical tasks can generate fears of failure and lower self-esteem [13]. Moreover, the impact of MLD in the onset of later psychopathological symptoms (e.g., anxiety disorder, depression) is well described [13]. MLD also requires extreme annual expenses to counteract its harmful societal consequences [14].

Nevertheless, current therapeutic options do not provide sufficient support to children with MLD and their families [13,15].

### 1.1. Neurocognitive Features of MLD

When a child is asked to solve an apparently simple arithmetic operation, multiple neurocognitive processes are rapidly encompassed. One way to improve mathematical abilities is by understanding such underlying neurocognitive functions.

On the cognitive level, experimental evidence suggests that “core” and “noncore” skills are impaired in individuals with MLD [16,17]. Core skills refer to the innate ability to process numerical information without consciously dealing with symbolic representations of numbers and are shared between humans (including infants and indigenous tribes who have little or no formal mathematical education [18,19]) and other species (for a review, see [20,21,22]). Core skills are considered to be specialized for such mathematical abilities as automaticity in processing numerical information, the ability to discriminate numerosities, representation of numerosities, mapping numbers onto space, and counting [23]. This sense of numerosity (also known as number sense [24]) has been widely proposed as a foundational basis for higher-order cognitive processes in the acquisition of abstract numerical concepts and in later achievements in mathematics [25,26,27,28].

In contrast, noncore skills are those that are crucial for numerical cognition but are not exclusive to the mathematical domain, such as executive functions (e.g., inhibitory control, working memory), visuospatial skills (e.g., mental rotation, visuospatial reasoning), and attention [29,30,31,32,33,34]. Theoretical evidence shows that working memory and visuospatial reasoning strongly predict mathematical achievements [35,36,37]. Working memory (likely the most widely studied domain-general function in relation to mathematical abilities [for a review, see 35]) has been linked to an individual’s ability with regard to fact retrieval, manipulation of operators, operands, and numerical facts [38,39]. Notably, a large community-based study by Judd and Klingberg [34] demonstrated that visuospatial training can be transferred to academic abilities and that reasoning ability and maintenance of spatial information are relevant for learning mathematics in young children.

On the neural level, an abnormal bilateral frontoparietal network has been consistently reported in individuals with MLD [40]. Specifically, atypical brain function has been found in the posterior parietal cortex (PPC) during numerical processing and calculation tasks [41,42] and in the temporoparietal areas during number facts, which requires the automatic retrieval of verbally stored numerical information from long-term memory [43]. Further, abnormal activation has been observed in the prefrontal regions, including the dorsolateral prefrontal cortex (dlPFC), regions that orchestrate noncore domain-general processes (such as working memory and problem solving) [44,45,46].

### 1.2. Current and New Treatment Perspectives in MLD

Given the profound negative effects of MLD, significant efforts have been made to develop effective interventions. In the last 20 years, educational programs [47,48,49], tutoring [50], and cognitive-based training programs [13] have been proposed to support children and adolescents with MLD. Although certain cognitive-based interventions have affected improvements [51,52,53], the results remain inconsistent and have not been examined systematically and integrated into a unique therapeutic practice [13]. Their efficacy and long-term outcomes remain unknown [52], and most studies are not supported by empirical and peer-reviewed research [54]. Collectively, the results for cognitive-based interventions lack high-quality standardized and evidence-based methods for clinical translation in interventional settings [13].

Extensive data from recent years on the neurobiology of MLD have increased the interest in neurostimulation approaches (e.g., transcranial random noise stimulation-tRNS), based on their potential to manipulate brain networks directly, alone or by enhancing the effects of other interventions [55]. tRNS is a safe, painless, cost-effective, affordable, portable, and user-friendly treatment option for the pediatric population. It is a polarity-independent form of transcranial electrical stimulation that entails the application of a weak current to the scalp at random intensities (e.g., ±0.5 mA) over a wide range of frequencies (from 0.1 to 640 Hz) [56].

A phenomenon, called stochastic resonance, would explain the mechanism of tRNS [57] and refers to the amplifying effect of adding noise to a signal that is too weak to exceed a threshold on its own [58]. However, its mechanism at the neural level remains under debate [59]. tRNS likely boosts long-term potentiation-like cortical plasticity by inducing the repetitive opening of sodium channels, shortening the hyperpolarization phase [58,59,60]. Moreover, a recent study in juvenile mice [61] has suggested that the effects of tRNS are attributed to modulation of the precursor of GABA, a neurotransmitter that is involved in neuroplasticity. tRNS could enhance excitability, which underlies the atypical bilateral frontoparietal network in children with MLD, with the potential to desynchronize dysfunctional rhythms.

Although the literature is increasingly highlighting the successful application of tRNS in enhancing arithmetic learning in healthy adults [62,63,64,65], our understanding of its real-world translation to clinical settings (particularly in atypically developing children) remains poor. Only a single-blind, between-subject pilot study has examined the effects of 4 sessions of tRNS over 10 days of cognitive training compared with placebo in children with MLD [66]. Twelve participants were pseudorandomized to receive active or sham tRNS over their bilateral dlPFCs while they performed a concomitant number line training. Active tRNS was beneficial compared with sham tRNS in improving arithmetic learning and performance while being safe and tolerable in the pediatric population [66].

Given the preliminary nature of the aforementioned study [66], open questions remain regarding the most suitable, effective, and feasible tRNS protocol for improving arithmetic abilities in a wide sample of children and adolescents with MLD (for example, the appropriate number of sessions, the most effective placement of electrodes (e.g., PPC vs. dlPFC), and the electrophysiological effects of tRNS).

Based on these encouraging preliminary results [66], large-scale and high-reproducibility clinical trials are urgently needed. According to the National Institute of Mental Health, insufficient reporting of study protocols is a critical aspect that hinders the development of therapeutic applications in neurostimulation [67].

### 1.3. Research Objectives

The overarching goal is to provide a scientific foundation for devising brain-directed and evidence-based treatments in children and adolescents with MLD. Based on insights from recent empirical research, this study addresses at least five gaps in research:(1)Examining the long-term safety and feasibility of a multisession tRNS protocol in the pediatric population (e.g., 10 sessions);(2)Determining the effects of the tRNS setup (over bilateral dlPFCs vs. bilateral PPCs) in improving long-lasting arithmetic learning and performance and neuropsychological and psychological measures compared with sham tRNS;(3)Testing whether and the extent to which arithmetic improvements after tRNS are related to neuropsychological changes;(4)Understanding whether and the extent to which changes in spontaneous EEG after tRNS are linked to arithmetic improvements;(5)Assessing whether and the extent to which improvements in arithmetic performance correlate with changes in the psychological function of children and their parents’ stress.

## 2. Materials and Methods

### 2.1. Ethical Committee

Ethical approval for this study was granted by the local research ethics committee (process number 1547_OPBG_2018) and was registered at ClinicalTrials.gov (ID: NCT04242680) on 28 January 2020. This study will be performed in accordance with the Declaration of Helsinki. The protocol adheres to the SPIRIT guidelines (Standard Protocol Items: Recommendations for Interventional Trials) and was prepared using the SPIRIT 2013 Checklist [68].

### 2.2. Study Setting and Participants

Recruitment will take place at the Child and Adolescent Neuropsychiatry Unit of Bambino Gesù Children’s Hospital in Rome. Participants will be enrolled during the daily clinical activities of the I.Re.Ne Lab (Innovation Rehabilitation in Neurodevelopment Lab) by psychologists, neuropsychiatrists, and speech therapists. Should that be the case, participants will be selected retrospectively from a comprehensive database, upheld by the direction of the Head of the Unit ([name]), which encompasses several hundred patients who have been assessed according to the good clinical practices per international guidelines for neurodevelopmental disorders. Research assistants will contact the selected participants by phone and e-mail to determine their interest in the project.

All participants and their parents will be fully informed of the procedures and purpose of the experiment, and the principal investigator will obtain written consent prior to participant entrance into the study. Participation will be solely voluntary.

The inclusion criteria are as follows: (1) participants of both genders, diagnosed with MLD per the Diagnostic and Statistical Manual of Mental Disorders, Fifth Edition (DSM-5) [1] and national recommendations [69], confirmed by experienced developmental psychiatrists and psychologists through their developmental history and extensive clinical examination; (2) the mathematical total quotient (MTq), per the Diagnostic Battery for Developmental Dyscalculia, Second Edition (BDE-2) [70], at least two standard deviations (SDs) below the mean (composite score ≤ 70); (3) intelligence quotient (IQ) ≥ 85; (4) age between 8 years and 6 months and 14 years and 11 months inclusive; and (5) normal or corrected-to-normal vision.

The exclusion criteria are: (1) the presence of another primary psychiatric diagnosis (e.g., depression, anxiety), autism, or attention deficit hyperactivity disorder; (2) a personal history of neurological/medical/genetic diseases; (3) a personal history or first-degree-relative history of epilepsy; (4) having undergone neuropsychological treatment for MLD in the year before the baseline screen; and (5) receipt of a CNS-active drug treatment.

### 2.3. Design, Randomization, and Blinding

The study will use a between-subject, randomized, double-blind, and sham-controlled design.

The screen for clinical eligibility will be completed on Day 0 of the trial, before the stratified randomization. Randomization occurs immediately after a participant completes the screening assessment, ensuring concealment of allocation. Participants will be allocated randomly to the following conditions: (1) Frontal Group (active tRNS over bilateral dlPFCs + cognitive training); (2) Parietal Group (active tRNS over bilateral PPCs + cognitive training); and (3) Sham Group (Sham tRNS over bilateral dlPFCs/PPCs + cognitive training). An independent researcher will perform the stratified randomization. The stratified randomization will use the minimal sufficient balancing method to prevent imbalances in baseline and will be based on the participants’ demographics (e.g., age, IQ, gender) and MTq [70].

The investigators who assess the participants will be blinded to the allocation, as will the participants and their parents. An independent researcher will maintain the randomization information until the data collection is completed. An emergency code break envelope will be provided to the principal investigator and will only be opened in the case of an emergency, such as a serious adverse event that requires knowledge of the interventions to manage the participant’s condition.

A baseline assessment (see Figure 1) will be completed on Day 1 (T0), before the interventions are administered. Participants will undergo combined interventions for 10 days (5 consecutive days per week for 2 consecutive weeks: from Day 1 to Day 5 and from Day 8 to Day 12). To minimize the influence of intracircadian variations, participants will attend stimulation sessions each day at the same time. Participants will also complete an assessment at the end of the interventions (Day 12, T1), 1 week later (Day 19, T2), and 3 months later (Day 102, T3). At the last follow-up, after the assessment, participants will be asked to guess their stimulation condition by the principal investigator.

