#### 2.5.1. Arithmetic Measures

Battery for Developmental Dyscalculia. The primary outcome of the study will be the Number Line subtest of BDE-2 [70]. BDE-2 [70] is a standardized clinical battery that is usually adopted in Italy for evaluating numerical cognition in children between the third grade of primary school to the third grade of secondary school. The battery encompasses several subtests that, in turn, are divided into three main quotients: number, calculation, and number sense and a comprehensive index of math abilities, the MTq. Higher scores indicate better outcomes and will be considered as an improvement.

Tempo Test Rekenen (TTR). TTR [78] measures the ability of children to correctly answer with no overt signs of calculations but automatically retrieving arithmetic information from long-term memory. The test consists of 200 written arithmetic number facts, divided into 5 subtests: addition (e.g., “2 + 3 = _”), subtraction (e.g., “8 − 3 = _”), multiplication (e.g., “5 × 9 =_”), division (e.g., “15 : 3 =_”), and mixed facts (e.g., “2 + 1 =_”; “2 − 1 =_”; “2 × 5 =_”; “4 : 2 =_”). Each subtest contains eight blocks of five operations that are presented with increasing difficulty, and participants are asked to solve as many arithmetic facts as possible in a maximum of 60 s for each subtest. The total number of correct answers is considered. Higher scores reflect better outcomes and will be considered as an improvement.

Math Processing Task. This task is selected from the Psychology Experiment Building Language program (http://pebl.sourceforge.net/, accessed on 5 October 2021) [79,80,81], which measures the ability of children to approximately quantify the numerical magnitude of arithmetic information that is automatically retrieved from the long-term memory. Arithmetic facts (addition and subtraction) with single-digit numbers are presented at the center of a PC screen in horizontal format as a solution from left to right, followed by an equal sign (e.g., “8 + 1 =_”; “9 − 3 =_”). Participants are required to determine whether the result is less or greater than five by pressing the left shift key (for results less than five) or the right key on the keyboard (for results more than five). Several arithmetic facts are presented in 60 s, and participants are required to respond within 1500 milliseconds (ms).

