### 3.2. Statistical Analysis

The Shapiro–Wilk test will be used to test the normality of the data, and Levene’s test will be performed to analyze the homogeneity of the variances. When the data are normally distributed and the assumption of homogeneity is not violated, parametric analyses will be computed. When one assumption is not met, nonparametric tests will be conducted or log-transformation of the distribution will be applied, if appropriate. When appropriate, sphericity will be verified by Mauchly’s sphericity test. When sphericity is not met, Greenhouse–Geisser correction will be applied.

Chi-square analysis will be used to compare groups with regard to demographics, blindness, and safety measures (categorical variables).

Linear mixed-effects models, which account for within-subject correlations more optimally than analysis of variance and automatically handle missing values, allowing maximum use of available data [93], will be run to compare groups for primary (continuous variables: number line subtest) and secondary outcomes (continuous variables: arithmetic, neuropsychological, and psychological measures). The R package lme4 v1.1–17 [94,95], which estimates model parameters using restricted maximum likelihood estimation and computed *p*-values per Satterthwaite’s method [96], will be used. The linear mixed-effects models will include Group (Frontal, Parietal, and Sham) and Time (T0, T1, T2, T3) as fixed factors and Participants as the random factor. Baseline performance will be included as a covariate in our model, because it allows us to make better adjustments for minor differences in pretreatment means. The same analysis will be performed for the training accuracy data, including Group (Frontal, Parietal, and Sham) and Day (from 1 to 10) as fixed factors and participants as the random factor.

Pearson’s correlation will be used to determine whether and the extent to which arithmetic improvements are related to changes in neuropsychological measures, psychological measures, and spectral power of EEG frequency bands at T1, T2, and T3 (from T0).

The statistical results will be corrected for multiple comparisons by Bonferroni’s correction where appropriate.

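### The outcome models omit the variables used to balance allocation: a possible loss of precision for between-group contrasts, though not for Group × Time

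*Protocol article*

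**What the plan says.** On allocation, section 2.3 states: "The stratified randomization will use the minimal sufficient balancing method to prevent imbalances in baseline". It adds that the procedure "will be based on the participants’ demographics (e.g., age, IQ, gender) and MTq". The demographics are given as examples, so the article does not close the list.

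On analysis, section 3.2 says that the mixed models for primary and secondary outcomes "will include Group (Frontal, Parietal, and Sham) and Time (T0, T1, T2, T3) as fixed factors and Participants as the random factor". One adjustment follows: "Baseline performance will be included as a covariate in our model". Age, IQ, gender and MTq are not model terms.

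Two further statements bear on the size of the effect. Section 2.5.1 says "The primary outcome of the study will be the Number Line subtest of BDE-2", and describes the same battery as yielding "a comprehensive index of math abilities, the MTq". Section 2.2 admits children with "age between 8 years and 6 months and 14 years and 11 months inclusive".

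**The concern.** Balancing makes the arms alike on the chosen variables, so those variables contribute less to the chance difference between arms than simple randomisation would allow. A model that omits them still counts their variation as error. The estimated standard error of a between-group difference is then larger than the true one, the test rejects a true null less often than 5%, and power is lost.

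The trial has little precision to spare: 34 children per arm at recruitment, or about 24 (34 × 0.70 = 23.8) if the assumed 30% dropout occurs. The variables are already collected, so any loss is avoidable.

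**Working it through.** **1. Which contrast the trial was sized on.** Inputs from section 2.6: f = 0.15, α = 0.05, 80% power, 3 groups, 4 measurements, N = 78. The correlation between visits is not stated; 0.5 is assumed, with sphericity. For the within-between interaction, λ = f²·N·m/(1 − ρ) = 0.0225 × 78 × 4 / 0.5 = 14.04, with (3 − 1)(4 − 1) = 6 and (78 − 3)(4 − 1) = 225 degrees of freedom. Power is 0.801, so 78 is reproduced. Under the same inputs the within-factor test would need 63 and the between-factor test 273. The sample size therefore matches Group × Time.

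**2. Group × Time contrast.** With T0 among the outcomes, this contrast compares changes from T0 between arms. A covariate that is constant over time is the same at both visits and cancels. Random-intercept models fitted to simulated data (78 children, 60 runs per scenario) agree. Without and with the covariate, the standard error was 0.2784 and 0.2784 when it explained 5% of total outcome variance, and 0.2770 and 0.2770 at 20%. With assumed dropout the largest change was 0.2869 to 0.2863, about 0.2%.

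**3. Between-group contrast adjusted for baseline.** Let R² be the share of between-participant outcome variance, left after baseline, that the balancing variables explain. The documents give no value, so a range is assumed.

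| R² | SE too wide: 1/√(1 − R²) − 1 | Type I error, near-perfect balance: 2[1 − Φ(1.96/√(1 − R²))] | Equivalent extra children: 1/(1 − R²) − 1 |
|---|---|---|---|
| 0 | 0% | 5.0% | 0% |
| 0.05 | 2.6% | 4.4% | 5.3% |
| 0.10 | 5.4% | 3.9% | 11.1% |
| 0.20 | 11.8% | 2.8% | 25% |

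**4. Simulation check.** The set-up was 78 children in three arms, tight adaptive balancing on four covariates, a baseline-adjusted comparison at one visit, and 2,000 runs. The Monte Carlo standard error near 5% is √(0.05 × 0.95/2000) = 0.005. At R² = 0.20 the mean model standard error was 0.2232 without the covariates and 0.1997 with them, a ratio of 1.118. Type I error was 0.029 without and 0.0505 with. At R² = 0.05 it was 0.048 and 0.0535, which the simulation cannot tell apart. Looser, threshold-triggered balancing schemes (settings assumed) gave 0.035 to 0.045 without the covariates at R² = 0.20.

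**5. How much baseline absorbs.** Suppose a covariate explains 20% of total outcome variance before baseline adjustment, and visits correlate 0.5. After adjustment its covariance with the outcome is 0.5 × √0.20 = 0.2236, its own variance is 1 − 0.20 = 0.80, and the outcome variance is 1 − 0.25 = 0.75. The remaining R² is 0.2236²/(0.80 × 0.75) = 0.083, so the standard error is 1/√(1 − 0.083) − 1 = 4.4% too wide. In the simulated mixed models with T0 only as a covariate, the standard error at T1 was 0.2417 without and 0.2324 with the covariate, 4.0% wider. At 5% of total variance it was 0.2410 and 0.2402, or 0.3%.

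**The case against.** A reader might infer that the omission makes every standard error in the trial too wide, including that of the test used for the sample size. The documents do not support this: the sample size matches Group × Time, and that contrast is essentially unchanged. The loss applies to the Group main effect and to group differences at follow-up with T0 used as a covariate. That reading remains open. Section 3.2 names a Group term, no Group × Time term, and a baseline covariate, and section 3.3 predicts better results than sham at T1.

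The remaining R² may also be close to zero, above all for the primary outcome. Baseline Number Line is already in the model and comes from the battery that yields MTq, and eligibility narrows both MTq (≤ 70) and IQ (≥ 85). This stands, and it is why the range starts at zero. The case is stronger for TTR (total correct) and Math Processing speed (milliseconds). No age conversion is stated for either, and ages run from 8.5 to 14.9 years, although each outcome's own baseline carries part of the age effect. Several other secondary outcomes are converted to weighted, z or t scores.

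The 2.8% figure could be mistaken for the trial's actual type I error. It is a limit: section 2.3 gives no imbalance threshold or allocation probability, and looser balancing brings the rate nearer 5%.

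Finally, the article condenses a fuller protocol, and a complete covariate list may stand in an analysis plan. That is possible. But the article does state the model and its covariate adjustment, and the balancing variables are not in it. The consequence is also only conservative, with no bias and no excess of false positives.

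**Conclusion.** The point holds for between-group contrasts. The stated models do not follow the allocation, and omitting prognostic balancing variables makes those tests somewhat conservative and less precise. The standard error is about 0–12% wider than needed if the variables explain 0–20% of the between-participant variance left after baseline. Type I error lies between 5% and a limit of 2.8% over that range, depending on the tightness of balance. Both the R² range and the balancing settings are assumptions. The Group × Time contrast with T0 as an outcome is essentially unaffected. The gain is likelier for raw-score secondary outcomes than for Number Line. This is an inexpensive improvement in efficiency, not a threat to validity.

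**What to change.** In section 3.2, add every variable used in the balancing algorithm as a fixed covariate in the primary and secondary models: age, IQ and screening MTq as continuous terms, and gender. Keep baseline performance in the model. Because section 2.3 introduces the demographics as examples, list the full balancing set there so that the two sections agree.

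The cost is one sentence in each section and about four degrees of freedom for the variables named. No new data are needed.
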